Doctors with Africa CUAMM is a non-governmental organization supporting health programs in different African countries. In the hospitals participating in the CUAMM projects, KMC represents a standard of care, but the heads of the babies often remain uncovered due to local habits or, more simply, to the unavailability of a cap. However, although WHO guidelines recommend the use of a cap/hat during KMC, the effect on neonatal temperature during the days and weeks following childbirth has not been previously studied. It is unknown whether covering the head of the neonate with a woolen cap during KMC may help temperature maintenance. The results of the present study will allow us to understand whether the use of a cap during KMC is effective and safe.

Previous studies suggest that neonatal heat loss following delivery may be reduced or prevented by the application of a woolen hat [6–8]. These studies assessed patients immediately after birth and for a short period. On the other hand, hyperthermia can be dangerous to the newborn infant and should also be avoided [9, 10].

To our knowledge, there are no previously published studies that have evaluated the effect of using a woolen cap in the course of KMC.

The aim of the present study will be to assess the effectiveness and safety of using a woolen cap in maintaining normothermia in low-birth-weight infants (LBWI) during KMC.

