### Procedure

After obtaining parental consent, all infants with a birth weight below 2500 g and who are candidates for KMC, based on the clinical decision of the attending physician, will be assigned to the KMC with a woolen cap group (KMC + cap) or to the KMC without a woolen cap group (KMC group). All the caps used for the study are handmade by a group of volunteers in Padova. The material (wool) was provided by CUAMM and sizes were standardized.

The procedure of initiating, maintaining and stopping the KMC will be based on WHO guidelines [5]. Mothers will be trained in monitoring the baby’s condition and in recognizing dangerous clinical signs during KMC [5]. The duration of the study will be until the patient’s discharge, with a maximum treatment duration of 7 days. In case of documented neonatal hypothermia (temperature below 36.5 °C) or hyperthermia (temperature above 37.5 °C) during the course of the study, the pre-warmed blanket will be added or removed. In case of maternal hyperthermia, we will ask the woman to wear lighter clothes. In these cases, neonatal and maternal temperatures will be measured every hour until the normal range is reached.

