### Primary outcome measure

The primary outcome measure will be whether the infants’ temperatures remain within the normal range (36.5–37.5 °C) in the course of KMC during the intervention. In all participants, axillary temperature will be measured with a digital thermometer (C202; Terumo, Tokyo, Japan) every 6 hours during KMC treatment. Maternal and room temperature will be registered at the same time. Room temperature will be measured at the same times (every 6 hours) by using the same wall thermometers (Oregon Scientific RMR262) in all three study sites.

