### Randomization

Eligible infants will be assigned to the KMC + cap or the KMC group in a 1:1 ratio according to a computer-generated, randomized sequence for each participating hospital. The randomized allocation will be concealed in double-enclosed, opaque, sealed, and sequentially numbered envelopes prepared at the University Hospital of Padua.

In the KMC room, the next sequential randomization envelope will be opened only when the attending operator considers the infant to be eligible. The assigned procedure (KMC + cap or KMC group) will be then performed. Cross-over will not be allowed. Analysis will be done as per intention-to-treat. A flow diagram of patient randomization is reported in Fig. 1.

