### Statistical analysis

Analysis will be performed as per intention-to-treat. Continuous data will be expressed as mean and standard deviation (SD) or median and interquartile range (IQR). The effect of the treatment on primary outcome will be assessed using a Poisson model adjusting for hospital and a set of clinically relevant confounders (maternal temperature, environmental temperature, birth weight, postnatal age). The logarithm of the number of measurements during hospital stay will be used as an offset, in order to take into account the different lengths of hospital stay of each participant. The effect of the treatment on the number of episodes of apnea will be assessed using a Poisson model adjusting for hospital and a set of clinically relevant confounders (neonatal and maternal temperatures, environmental temperature, birth weight, postnatal age). The logarithm of the number of measurements during hospital stay will be used as an offset. The effect of the treatment on binary secondary outcome (sepsis and mortality before hospital discharge) will be assessed using a logistic regression model adjusting for hospital and birth weight. The effect of the treatment on continuous secondary outcome (in-hospital growth) will be assessed using a regression model adjusting for hospital. Statistical analysis will be performed using R 3.2.2 software (R Foundation for Statistical Computing, Vienna, Austria) [11]. A *p* value less than 0.05 will be considered statistically significant.

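### The apnea model adjusts for neonatal temperature, a post-randomization variable the cap is meant to change, so it does not estimate the cap's total effect on apnea

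*Protocol article*

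**What the plan says.** All references are to the protocol article. The Statistical analysis section declares intention-to-treat and specifies two Poisson models.

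- **Primary outcome model:** adjusted for hospital and "maternal temperature, environmental temperature, birth weight, postnatal age".
- **Apnea model:** adjusted for hospital and "neonatal and maternal temperatures, environmental temperature, birth weight, postnatal age".

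Both covariate lists are described as confounders. Both models use the log of the number of measurements per infant as offset; for the primary model the stated purpose is to allow for differing lengths of stay.

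The primary outcome is "whether the infants’ temperatures remain within the normal range (36.5–37.5 °C) in the course of KMC during the intervention", with the infant's temperature taken "every 6 hours during KMC treatment". The same section adds: "Maternal and room temperature will be registered at the same time". Under Randomization, "the next sequential randomization envelope will be opened only when the attending operator considers the infant to be eligible", and the assigned procedure follows. No temperature reading before that point is described. The Background gives the aim as to "assess the effectiveness and safety of using a woolen cap in maintaining normothermia in low-birth-weight infants (LBWI) during KMC".

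**The concern.** In a randomized comparison, a variable measured after allocation that treatment is designed to alter is not a confounder. Neonatal temperature is such a variable here. Holding it fixed in the apnea model asks whether the cap affects apnea among infants who reach the same temperature. That is a different question from the effect of being assigned a cap.

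Two things follow. A benefit acting through warmth, or a harm acting through overheating, is taken out of the treatment coefficient. And if an unmeasured feature such as illness affects both temperature and apnea, conditioning on temperature links that feature to the arm and adds bias.

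The stated aim covers safety as well as effectiveness, and apnea is the first secondary outcome listed, so the result will be read as evidence on safety. Maternal temperature raises a weaker form of the same question in both models.

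**Working it through.** There is no stated figure to reproduce: the protocol gives no apnea rate or effect size, and its sample size of 300 was not derived from a calculation. The timing and role of each covariate come from the text; the sizes below rest on assumptions.

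**1. Covariates by timing and role**

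- Hospital and birth weight are fixed before allocation. Postnatal age is too, if taken at randomization.
- Neonatal temperature: six-hourly during KMC, so after allocation; basis of the primary outcome and target of the cap.
- Maternal temperature: same time points, so after allocation; also subject to action during follow-up ("In case of maternal hyperthermia, we will ask the woman to wear lighter clothes").
- Room temperature: same time points, but the cap is unlikely to affect it.

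**2. Apnea, by algebra**

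Assume the cap raises temperature by 0.2 °C and the log apnea rate falls by 1.5 per °C.

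- Total rate ratio, all through temperature: exp(−1.5 × 0.2) = exp(−0.3) = 0.74.
- With temperature held fixed, nothing remains: exp(0) = 1. A simulation of this case gave 0.740 unadjusted and 0.992 adjusted.
- Same total, half through temperature: the remaining part is exp(−0.15) = 0.86.

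**3. Apnea, by simulation over a range**

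Assumptions: 150 infants per arm, 8 to 28 readings each, 0.03 apneas per reading, full mediation, 300 replicates per setting. Hospital, room temperature, birth weight and age were left out.

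| Cap effect (°C) | Log rate per °C | True ratio | Without temperatures | With neonatal and maternal temperature |
|---|---|---|---|---|
| 0.1 | −1 | 0.905 | 0.901 | 0.996 |
| 0.1 | −2 | 0.819 | 0.815 | 0.998 |
| 0.2 | −1 | 0.819 | 0.821 | 1.005 |
| 0.2 | −2 | 0.670 | 0.660 | 0.986 |
| 0.3 | −1 | 0.741 | 0.727 | 0.980 |
| 0.3 | −2 | 0.549 | 0.541 | 0.981 |

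At a true ratio of 0.670, the proportion of replicates with p < 0.05 was 71% without the temperatures and 5% with them. When an unmeasured frailty affecting both temperature and apnea was added (0.2 °C, −1 per °C, true ratio 0.82), the estimate was 0.81 without the temperatures and 1.18 with them, so the direction reversed.

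**4. Primary model and maternal temperature**

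Assumption: the log-odds of an in-range reading rise by 1 per °C of maternal temperature.

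| Cap effect on maternal temperature (°C) | Ratio without it | Ratio with it |
|---|---|---|
| 0 | 1.07 | 1.07 |
| 0.05 | 1.09 | 1.08 |
| 0.1 | 1.11 | 1.07 |
| 0.2 | 1.15 | 1.07 |

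With no cap effect on the mother there is no bias. With one, the adjusted model omits that part of the total effect.

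**5. Apnea offset**

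- If only the four scheduled daily readings count, measurements = 4 × days and log(measurements) = log(days) + log 4. The constant goes into the intercept and the rate ratio is the same as with days.
- The Procedure section also requires hourly readings after an out-of-range value. If these counted, an infant with 8 excursions of 3 extra readings each over 7 days would have 28 + 24 = 52 readings instead of 28, and 52/28 = 1.86. The 8 and the 3 are assumed.

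**The case against.** The strongest reply is that only one part of this is certain.

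- **Primary result.** A reader might infer that the primary treatment effect is biased because its model includes a post-randomization covariate. The documents do not support that. Nothing in them says a cap on the infant changes the mother's temperature, and the clothing rule applies to both arms. Skin-to-skin contact and unmasked staff make an influence possible but do not establish it. This objection stands.
- **Size.** The near-null adjusted ratios follow from assuming full mediation. A reader might infer that any real effect on apnea would be reported as none; that needs the whole effect to pass through temperature, which the documents do not show. This also stands, and it limits the magnitude. It does not rescue the model, since any mediated part is still removed.
- **Offset.** A reader might infer that exposure is overstated 1.86-fold. That holds only for the invented infant, and only if hourly rechecks count as measurements, which the text does not say. A biased comparison would further need the rechecks to differ between arms.
- **Which temperature.** The covariate could be an enrolment value. Only readings during KMC are described, so this rescue has no support in the text.
- **Room temperature.** Nothing here argues against keeping it.

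**Conclusion.** The concern holds for neonatal temperature in the apnea model. As written, that model does not estimate the total effect of assignment to the cap, although the plan declares intention-to-treat. This rests on the protocol's own account of what the cap targets and when temperature is read, and on no assumed number.

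The size is not known. Under full mediation, true rate ratios from 0.55 to 0.90 are estimated as about 1; under partial mediation the attenuation is smaller; with shared illness the direction can reverse. All of these depend on assumed inputs.

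For maternal temperature the supportable statement is conditional: it is not a confounder of a randomized comparison, and it may bias either model if the cap or unmasked care alters it. The offset needs only a clear definition.

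The certain error concerns one secondary outcome and does not by itself touch the primary conclusion. It should be corrected before analysis, but it is not a critical fault.

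**What to change.** 1. Remove neonatal temperature from the apnea model.
2. In both count models, drop concurrent maternal temperature from the main analysis. Keep hospital, birth weight and postnatal age, stating that age is taken at randomization. Room temperature may stay.
3. Present any model with concurrent neonatal or maternal temperature as a sensitivity or exploratory analysis, and do not call these variables confounders.
4. Use log(days observed) as the apnea offset or, equivalently, the log of the number of scheduled six-hourly readings, and state that hourly rechecks are not counted.

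The cost is analysis wording and no new data. Dropping maternal temperature should lose a little precision; the documents do not allow the amount to be calculated. Replacing it with an enrolment value is not a safe alternative: no such reading is described, and enrolment began in January 2016, so the values may not exist.

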### Setting

The study will be conducted at three hospitals that have three different levels of healthcare in three African countries where Doctors with Africa CUAMM has ongoing projects on maternal-neonatal health. They are:Central Hospital of Beira in Mozambique (5555 deliveries – CUAMM data 2013), which is a governmental hospital (III level) (Mozambique: neonatal deaths, 34 % of all under-5 deaths; neonatal mortality rate: 30 per 1000 live births; source: *Countdown to 2015, The 2014 Report*) (http://www.mediciconlafrica.org content/uploads/sites/2/2015/09/Health_and_Devel_71_giu15-BASSA.pdf)St. Luke Wolisso Hospital in Ethiopia (3323 deliveries – CUAMM data 2013), which is a no-profit zonal hospital (II level) (Ethiopia: neonatal deaths, 43 % of all under-5 deaths; neonatal mortality rate: 29 per 1000 live births; source: *Countdown to 2015, The 2014 Report*) (http://www.mediciconlafrica.org content/uploads/sites/2/2015/09/Health_and_Devel_71_giu15-BASSA.pdf)Aber Hospital in Uganda (1872 deliveries – CUAMM data 2013), which is a no-profit rural hospital (I level) (Uganda: neonatal deaths, 33 % of all under-5 deaths; neonatal mortality rate 23 per 1000 live births; source: *Countdown to 2015, The 2014 Report*) (http://www.mediciconlafrica.org content/uploads/sites/2/2015/09/Health_and_Devel_71_giu15-BASSA.pdf)

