### Sample size

The lack of information about this topic (temperature during KMC in the specific scenario of head covering) prevented us from obtaining a mathematical estimation of the sample size. Thus, the sample size was arbitrarily defined in order to take into account the enrollment rate of each hospital. According to the number of admissions in each participating hospital, we decided to enroll a total of 300 subjects (150 in the cap group and 150 in the uncovered head group) as follows: 150 at Central Beira Hospital, 90 at St. Luke Wolisso Hospital and 60 at Aber Hospital.

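### If deaths are as few as the quoted national rates imply (about 8), the default Wald test in the planned mortality model rejects only 1–2% of the time at a nominal 5%

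*Protocol article*

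**What the plan says.** The Statistical analysis section of the Protocol article handles the two binary secondary outcomes, sepsis and death before discharge, with one method: the treatment effect "will be assessed using a logistic regression model adjusting for hospital and birth weight". With three hospitals the model has four coefficients beyond the intercept: treatment, two hospital terms and birth weight. The threshold is p < 0.05 and the software is R 3.2.2. The section does not say whether estimation is by maximum likelihood or penalised likelihood, or whether the test is Wald or likelihood ratio.

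The article gives no expected number of deaths. The Sample size section says that "the sample size was arbitrarily defined in order to take into account the enrollment rate of each hospital" and sets targets of "150 at Central Beira Hospital, 90 at St. Luke Wolisso Hospital and 60 at Aber Hospital". The only mortality rates are in the Setting section, as country background: "neonatal mortality rate: 30 per 1000 live births" for Mozambique, "neonatal mortality rate: 29 per 1000 live births" for Ethiopia and "neonatal mortality rate 23 per 1000 live births" for Uganda.

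**The concern.** Ordinary logistic regression relies on large-sample theory, and the sample that matters is the number of events. With few deaths the Wald standard error grows along with the estimate, so even a lopsided split between arms may not reach significance. If one arm has no deaths, the maximum-likelihood odds ratio is zero or infinite.

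Mortality is the gravest of the secondary outcomes, and the stated aim covers safety as well as effectiveness. A test that rejects far less often than its nominal level loses power that was scarce to begin with. Caregivers and outcome assessors are unmasked, so a small-sample method chosen after the deaths are known would be open to challenge.

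**Working it through.** **Expected deaths.** The protocol has no figure of its own to reproduce. Multiplying each site target (Sample size) by its national rate (Setting):

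150 × 0.030 + 90 × 0.029 + 60 × 0.023 = 4.50 + 2.61 + 1.38 = 8.49.

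With four coefficients that is 8.49 / 4 ≈ 2.1 deaths each. The simulated 95% range is 4 to 15 deaths.

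**Why Wald fails here: an unadjusted check with 8 deaths, 150 per arm.**
- Split 7 v 1: log odds ratio = ln[(7 × 149) / (1 × 143)] = ln 7.29 = 1.987. SE = √(1/7 + 1/1 + 1/143 + 1/149) = 1.075. z = 1.85, p ≈ 0.065, so not significant.
- Split 8 v 0: the estimate and its SE diverge, so Wald does not reject.
- More even splits give smaller z.

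No split of 8 deaths can therefore be significant, and the exact size is 0. Fisher's exact test has size 0.7% at 8 deaths, so an exact unadjusted test does not cure the conservatism.

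**Planned model, simulated at the quoted rates with no treatment effect** (1:1 within hospital; two-sided 0.05 assumed, as sidedness is not stated). Run A used 6000 trials with birth weight of mean 1.8 kg, SD 0.35 kg and log-odds slope −1 per kg. Run B used 4000 trials and a birth-weight log odds ratio of −0.5 per SD. Run C is a further run at the same rates. The birth-weight effects are assumptions.

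| Run | ML Wald | Ordinary likelihood ratio | Firth, profile test |
|---|---|---|---|
| A | 1.25% | 5.9% | not computed |
| B | 1.6% | 7.3% | 4.4% |
| C | 1.9% | 7.7% | 4.8% |

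Firth estimation with a Wald test reached only 2.0% in run A, so the profile test is an essential part of the remedy.

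**Power at a treatment odds ratio of 2, quoted rates.** Run B (2000 trials): Wald 15.0%, Firth profile 19.2%. Run C: 15.6% and 19.5%.

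**Dependence on the true rate** (run A, no effect, 3000 trials per row).

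| Multiple of quoted rates | Deaths | ML Wald | Arm with no deaths |
|---|---|---|---|
| 0.5 | 4.3 | 0.2% | 21% |
| 1 (6000 trials) | 8.5 | 1.25% | 2.3% |
| 2 | 17 | 4.0% | <0.1% |
| 3 | 26 | 4.7% | 0% |
| 5 | 43 | 4.8% | 0% |

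Run B had an arm with no deaths in 3.2% of trials at the quoted rates. At twice the rates (1500 trials per setting) it gave Wald v Firth sizes of 3.3% v 3.9% and power of 32.1% v 33.5%.

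**A hospital with no deaths.** P = (1 − rate)^n: Beira 0.970^150 = 1.0%, Wolisso 0.971^90 = 7.1%, Aber 0.977^60 = 24.8%. At least one: 1 − 0.990 × 0.929 × 0.752 ≈ 31%. In a constructed dataset of 8 deaths with none at the third hospital, that hospital's coefficient diverged (−21.4, SE about 16,800). The treatment result was identical with and without its infants: log odds ratio 0.527, SE 0.743, p = 0.478. In run A, whenever a hospital had no deaths but both arms had some, the treatment SE never diverged and every fit converged.

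**The case against.** The strongest reply is that the article prescribes a model, not a test. Maximum likelihood and Wald are software defaults read into it. The choice of test and a sparse-data fallback are ordinary SAP content, and a journal article condenses. This stands in part: the article does not prescribe a Wald test, and a SAP may already deal with it. But the stated analysis, read in the ordinary way, behaves badly if deaths are this few. The obvious alternative, a likelihood-ratio test of the same model, is no clean answer either, since it ran at 5.9–7.7% in the three runs.

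Second, 8 deaths is not a planning figure. The rates are national and cover all live births. The trial enrols singletons below 2500 g without major malformations who are KMC candidates, and counts deaths before discharge. Low birth weight raises the rate and fitness for KMC lowers it. This stands fully, and it makes the size of the problem conditional on an event rate the article does not give.

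Third, a reader might infer that the analysis fails whenever a hospital has no deaths, which would happen in about 31% of trials at these rates. It does not. Only that hospital's own coefficient diverges (or the intercept, if it is the reference), and the treatment estimate is untouched. The treatment estimate breaks down when an arm has no deaths, which is much rarer at the quoted rates.

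Finally, mortality is secondary, power of 15% or 19% is inadequate either way, and a monitoring board reviews every death. Detection of harm therefore does not rest on this p-value alone.

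**Conclusion.** The point holds as a minor one about the mortality analysis. If mortality is near the quoted national rates, the default Wald test of treatment has a size of about 1–2% at a nominal 5%, and the treatment odds ratio is zero or infinite in about 2–3% of trials. At half those rates both problems worsen; at two to three times them they largely disappear. The conclusion rests on the illustrative rates, a two-sided test, assumed birth-weight effects, and the default reading of the stated model.

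The documents do not support a claim that the protocol expects 8 deaths, that it specifies a Wald test, or that an empty hospital invalidates the comparison. What remains is an avoidable weakness with a cheap remedy that does no harm if deaths prove more frequent.

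**What to change.** In the Statistical analysis section, and in the SAP if there is one, prespecify for both sepsis and mortality a Firth penalised logistic regression with treatment, hospital and birth weight, reporting the profile penalised-likelihood confidence interval and test. Apply it whatever the observed number of events: a switch triggered by low counts would itself be data-driven, and the article gives no sepsis rate from which to set a threshold. Also tabulate deaths by arm and hospital, so that readers can see how little information the odds ratio rests on.

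The cost is one sentence and an available R package, with the covariates unchanged. The odds ratio is shrunk slightly towards 1. No loss of power was seen at the higher rates examined. The change does not make the trial adequately powered for mortality, and the report should say so.

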### Inclusion criteria

Infants satisfying the following inclusion criteria will be eligible to participate in the study:Birth weight below 2500 g (and)Candidate to KMC treatment (and)Parental consent: a written informed consent will be obtained by a member of the neonatal team involved in the study from a parent or guardian before KMC treatment

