### Confidentiality

Only the local PI will have access to the Excel database with an assigned personal account and password. Subjects will be identified by sex, birth date, and assigned trial number, during and after the trial, in accordance with personal data protection law.

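### The in-hospital growth model adjusts for hospital only; adding birth weight and postnatal age at randomization would sharpen a secondary comparison that is already unbiased

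*Protocol article*

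**What the plan says.** The Statistical analysis section of the protocol article fixes a covariate set for each outcome.

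- **Primary outcome:** Poisson model with hospital and "clinically relevant confounders (maternal temperature, environmental temperature, birth weight, postnatal age").
- **Apnea:** Poisson model with hospital and "neonatal and maternal temperatures, environmental temperature, birth weight, postnatal age".
- **Sepsis and mortality:** the treatment effect "will be assessed using a logistic regression model adjusting for hospital and birth weight".
- **Growth:** the "continuous secondary outcome (in-hospital growth) will be assessed using a regression model adjusting for hospital".

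Secondary outcome measures defines growth as the infant's weight at discharge, not as a gain from birth or from entry. Inclusion criteria reads "Birth weight below 2500 g (and)Candidate to KMC treatment (and)Parental consent". Neither it nor Exclusion criteria limits age at entry. Data collection does not name postnatal age, but two models require it, and Confidentiality states that "Subjects will be identified by sex, birth date, and assigned trial number".

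**The concern.** Infants enter when the physician judges them ready for KMC, and Background says this depends on their no longer needing treatment such as oxygen or intravenous fluids. Age at entry can therefore differ between infants. An infant's age at entry plausibly predicts how much of the early weight course has passed by discharge. It is fixed at randomization and the cap cannot alter it.

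The growth model uses neither this variable nor birth weight, although birth weight appears in every other model of the section. Discharge weight will vary widely simply because infants below 2500 g start from different weights. A model with hospital alone leaves that variation in the residual. At stake is the width of the confidence interval for one secondary outcome, in a trial whose size was set by enrolment capacity and not by a power calculation (Sample size).

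**Working it through.** **Inputs from the protocol article.** 300 infants, 150 per arm; 150, 90 and 60 by hospital (both sums give 300); 1:1 allocation from a separate sequence per hospital; significance level 0.05, taken as two-sided. The article gives no SD, correlation, sepsis rate or power, so there is no figure of its own to reproduce. Everything below is a range under stated assumptions.

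**Growth, one added covariate.** The hospital-only model has 4 parameters (intercept, treatment, two hospital terms), so 296 residual degrees of freedom. Adding a covariate with partial correlation r to discharge weight leaves 295:

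SE ratio = √[(1 − r²) × 296/295]

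Power is for a difference of 0.3 residual SD (assumed): Φ(0.3 / (SE ratio × √(2/150)) − 1.96).

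| r | SE ratio | Power |
|---|---|---|
| hospital only | 1 | 73.8% |
| 0.05 | 1.000 | 73.8% |
| 0.1 | 0.997 | 74.1% |
| 0.2 | 0.982 | 75.4% |
| 0.3 | 0.956 | 77.6% |
| 0.5 | 0.868 | 85.0% |
| 0.7 | 0.715 | 95.3% |
| 0.9 | 0.437 | >99.9% |

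If the covariate is useless (r = 0), the ratio is √(296/295) = 1.0017, a loss of about 0.2%.

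**Reading the table for age.** A cut of 0–6% from age alone corresponds to r up to about 0.35: 0.94² × 295/296 = 0.881, and √(1 − 0.881) ≈ 0.35. With birth weight already in the model the factor is 295/294. A cut of 1–12% then corresponds to r of about 0.15 to 0.48: 0.99² × 294/295 = 0.977 gives 0.15, and 0.88² × 294/295 = 0.772 gives 0.48. The share is larger in the second case because birth weight has removed variation that age does not explain.

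**Reading the table for birth weight.** At an assumed correlation of 0.7–0.9 the SE falls by 1 − 0.715 = 28% to 1 − 0.437 = 56%. At 0.7, adding age as well would take the ratio from 0.715 to between 0.715 × 0.99 = 0.71 and 0.715 × 0.88 = 0.63. Birth weight does most of the work.

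**Sepsis, age added to hospital and birth weight.** Simulation of 300 infants in hospitals of 150/90/60, 1:1 within hospital, true cap odds ratio 0.5, 1,500 runs per scenario:

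| Control sepsis rate | Age log-OR per SD | Ratio of SEs (with/without age) | Power without → with age |
|---|---|---|---|
| 5% | 0 | 1.003 | 14.1% → 13.9% |
| 5% | 0.7 | 1.018 | 12.5% → 13.1% |
| 5% | 1.0 | 1.037 | 12.7% → 14.4% |
| 10% | 0 | 1.003 | 31.6% → 32.1% |
| 10% | 0.7 | 1.026 | 30.9% → 31.0% |
| 10% | 1.0 | 1.053 | 29.9% → 33.3% |
| 20% | 0 | 1.002 | 55.5% → 55.7% |
| 20% | 0.7 | 1.038 | 51.1% → 53.4% |
| 20% | 1.0 | 1.076 | 45.8% → 50.4% |

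Larger cap effects (odds ratio 2.5 at a 10% control rate, 0.4 at 20%; 4,000 runs each) give the same pattern:

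- Age OR 0.5 per SD (log-OR −0.69): 73.8% → 76.5% and 72.5% → 75.5%.
- Age OR 0.33 per SD (log-OR −1.11): 66.0% → 72.2% and 65.6% → 72.2%.

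The SE of the log-odds ratio rises. Any power gain comes from the estimate moving away from zero.

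**Events available for sepsis.** At overall rates of 5–10% there are 15–30 events. That is 15/4 = 3.8 to 30/4 = 7.5 per parameter now counting treatment, hospital and birth weight, and 15/5 = 3.0 to 30/5 = 6.0 with age added.

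**The case against.** The strongest reply is that covariates in secondary models are a matter of choice. Different sets for different outcomes are no contradiction, and the plan attaches its relevance label to the temperature and apnea models, without saying that age matters for sepsis or discharge weight. Randomization protects the comparison either way. The spread of entry ages is unknown, since consent precedes KMC and KMC may start early, so the gain from age could be close to nil. All of this stands. It limits the point to efficiency and to a low priority. It does not remove it for growth: the model is stated outright, not left to another document, and 300 infants can carry two more terms in a linear regression without measurable loss.

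A reader might go further and infer that precision on sepsis is being thrown away for nothing. The documents do not support that. In a logistic model the added term widens the standard error, the power gain is small for a weak or moderate age effect, and with possibly 15–30 events a compact model for sepsis is defensible. A reader might also take it that age is listed as recorded data. It is not named in Data collection; its availability follows from the two models that use it and from the birth date.

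**Conclusion.** The point holds for growth, as a minor improvement. The growth regression leaves out two baseline predictors that the plan uses elsewhere. Age would cut the standard error by about 0–6% alone and about 1–12% given birth weight; birth weight would cut it by about 28–56% at a correlation of 0.7–0.9. These figures rest on assumed correlations, because the documents contain no growth data. There is no bias and no invalid test.

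For sepsis, adding age is optional. The gain is about 0–4 power points for a null to moderately strong age effect, allowing for simulation error, and about 2–7 points only if age is very strongly prognostic (log-OR near 1 per SD).

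**What to change.** In Statistical analysis, change the growth model to a linear regression of discharge weight on treatment, hospital, birth weight and postnatal age at randomization (days, continuous). Derive age from birth date and date of randomization. Age at discharge should not stand in for it, because it is observed after allocation and the abstract lists it as an outcome. With birth weight in the model, the treatment coefficient is the same whether the outcome is written as discharge weight or as gain since birth, which also suits the outcome's name better.

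The cost is two degrees of freedom out of 296 and one sentence of text, with no new patients and no item beyond those the primary and apnea models already need. The change should be made before allocation is revealed to the statistician. The sepsis and mortality models can stay as they are. If the team wants age in the sepsis model, that should be decided on the pooled number of events, without looking at results by arm.
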